# Pulp repair response after the use of a dentin-pulp biostimulation membrane (BBio) in primary teeth: study protocol for a randomized clinical trial

**DOI:** 10.1186/s13063-020-04785-2

**Published:** 2020-10-22

**Keywords:** Vital pulp therapy, Pulpotomy, Chitosan, Tooth, Deciduous, Pulp

## Abstract

**Background:**

Vital pulp therapy aims at maintaining the pulp tissue injured but vital. Thus, the use of capping materials that induce tissue regeneration is a great current trend. This study aims to evaluate clinically and radiographically the pulp repair after the use of dentin-pulp biostimulation membrane in primary teeth.

**Methods:**

Four hundred and sixty-eight teeth from children aged between 5 and 9 years old, both genders, with deep caries lesion with pulp involvement, but no furcal impairment and any sign of necrosis will be selected. The vital pulp therapy will be performed with mineral trioxide aggregate (control group) and dentin-pulp biostimulation chitosan membrane (BBio group). The clinical and radiographic outcomes will be assessed at 12 and 24 months after treatment. The thickness of the dentin barrier will be verified through *Image J2* software. The Wilcoxon signed rank test and Mann-Whitney test will respectively compare the intra- and intergroup clinical and radiographic outcomes. Paired *t* test and independent *t* test will respectively compare the intra- and intergroup radiographic measurements. The logistic regression will be applied, and the degrees of this association will be measured using odds ratio (OR) and 95% confidence interval (95% CI).

**Discussion:**

Therefore, this study protocol aims at new perspectives of vital pulp therapy of primary teeth by employing new easy-handling, low-cost material to keep viable the pulp tissue capable of regenerating and maintain the physiological process of deciduous tooth exfoliation.

**Trial registration:**

Brazilian Registry of Clinical Trials RBR-6vr58b. Registered on 17 February 2019.

## Background

Currently, endodontic treatments focus on reducing the pulp devitalization by either preserving or regenerating the pulp tissue after the pathologic alterations [1–4]. Regenerative procedures use materials to replace the cells or induce the remnant cells to differentiate in new pulp cells [4, 5].

Mineral trioxide aggregate (MTA) is the gold-standard material for clinical procedures of vital pulp therapy of primary teeth because of higher success rates in systematic reviews and meta-analysis [6–10]. Despite its biocompatibility, MTA has a longer setting time, difficult handling, high cost, and a potential for tooth discoloration [9, 11–13].

Technology and innovation aid in developing capping materials tailored for vital pulp repair and regeneration [14–19]. Thus, the search for new bioactive, biodegradable, and nontoxic material is constant [4, 20]. In this scenario and given its commonness regenerative, anti-inflammatory properties, and biocompatibility, chitosan, a natural polymer derivative of chitin, has found several applications in dentistry nowadays [21–23].

Recent studies point out that biochemical and biophysical characteristics of polymers and membranes have great potential for application in different dentistry fields [24–26]. Due the biochemical properties of chitosan and the ability to interact and stimulate pulp cells, chitosan has been exploited in association with other materials to produce new bioactive pulp dressings [23, 27]. Local antimicrobial drug delivery systems may eradicate the pathogenic microbiota or modulate the inflammatory response by decreasing the tissue destruction [4].

After the successful in vitro biophysical and biological characterization of an intraoral multilayer membrane with chitosan [25, 26], this study will aim to verify pulp repair response after the use of a new dentin-pulp biostimulation material in vital pulp therapy of primary teeth. The null hypothesis is that the new dentin-pulp biostimulation material will result in comparable clinical and radiographic success rate of MTA.

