### Sample size

The minimum sample size calculation was performed based on data from a previous study that found clinical and radiographic success of 94.73% for teeth treated with MTA [14]. For the sample calculation, alpha and beta errors of 5% and 20% will be respectively considered. The sample size also provides 80% power. The sample will be of 143 teeth per group to detect significant differences. A dropout rate of 20% will be estimated, and then, the number of eligible teeth will be 234 per group.

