### Statistical methods

All data will be analyzed using the PASW Statistics 21 software (SPSS) (IBM, Armonk, NY, USA). During all study, two trained and calibrated examiners will evaluate the treated teeth clinically and radiographically. Inter- and intra-examiner reliability will be verified by casual and systematic error. The Kolmogorov-Smirnov test will be adopted to test the normality of continuous variables, which will be expressed as median for the variables with a non-normal distribution and a mean value ± SD for the variable with a normal distribution. The Wilcoxon signed rank test will compare the clinical and radiographic outcomes over period. The Mann-Whitney test will compare the clinical and radiographic outcomes between groups. Paired *t* test will be used to compare the radiographic measurements over time. Independent *t* test will compare the radiographic measurements between groups. The level of significance of 5% will be adopted for all comparisons. The logistic regression will be applied, and the degrees of this association will be measured using odds ratio (OR) and 95% confidence interval (95% CI).

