The limitations of the present study include the disadvantages of noncompliance and high dropout rates, and the obstacle to control the period of follow-up. These disadvantages result in investigations with small sample size and the follow-up time. Further studies should be conducted, and the results should be confirmed through longer-term follow-up periods. The measurement of the dentin barrier after procedures of pulp therapy may have some limitations. This method will be used to avoid mistaken measurements due to the difficulty in evaluating the exact thickness of the dentin barrier and the overlapping of the radiographic image of the roots. One other bias of this present study will be the blinding of the operator. Although it is not possible to blind the operator during capping material application, we believe that this will not interfere in the study outcomes. Therefore, this study protocol aims at new perspectives of vital pulp therapy of primary teeth by employing new easy-handling, low-cost materials to keep viable the pulp tissue capable of regenerating and maintain the physiological process of deciduous tooth exfoliation.

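### Comparable success is the null hypothesis, but the plan has only difference tests and an odds ratio without a margin, so a non-significant result cannot support comparability

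*Protocol article*

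**What the plan says.** The Background section describes the comparator in these words: "Mineral trioxide aggregate (MTA) is the gold-standard material for clinical procedures of vital pulp therapy of primary teeth". It then sets the hypothesis: "The null hypothesis is that the new dentin-pulp biostimulation material will result in comparable clinical and radiographic success rate of MTA".

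The Sample size section starts from an earlier study that "found clinical and radiographic success of 94.73% for teeth treated with MTA" and says that "alpha and beta errors of 5% and 20% will be respectively considered". It concludes: "The sample will be of 143 teeth per group to detect significant differences". It gives no BBio success rate, detectable difference or margin.

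The Statistical methods section says: "The Mann-Whitney test will compare the clinical and radiographic outcomes between groups". Radiographic measurements are compared between groups with an independent t test. It adds: "The level of significance of 5% will be adopted for all comparisons". It also plans logistic regression with an odds ratio and 95% CI, but attaches no decision criterion to that interval. Whether tests are one- or two-sided is not stated.

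The Discussion gives the purpose of the trial as "employing new easy-handling, low-cost materials to keep viable the pulp tissue capable of regenerating".

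**The concern.** A significance test can reject its null hypothesis but cannot establish it. Here the null is the statement a reader would most like to see supported: that a new material performs about as well as the established one. The stated drawbacks of MTA are setting time, handling, cost and discoloration, not low success. With MTA success at 94.73%, BBio can exceed it by at most 100 − 94.73 = 5.27 points. A finding that BBio is not meaningfully worse is therefore a likely use of the results, and no planned analysis has a criterion for reaching it.

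The direction of the error also matters. Losing participants lowers power, which makes it more likely that a null worded as comparability is retained. The Discussion itself names high dropout as a limitation.

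**Working it through.** **Inputs.** MTA success 94.73%, alpha 5%, power 80%, 143 per group and 234 per group enrolled (all from Sample size). After the stated 20% dropout, 234 × 0.8 = 187 per group. Two-sided testing and equal allocation are assumptions.

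**1. The plan's own figure.** The 143 cannot be derived from the stated inputs, because the BBio rate is missing. Solving backwards with n = [1.96·√(2p̄(1−p̄)) + 0.842·√(p1(1−p1) + p2(1−p2))]² / (p1−p2)²:
- p1 = 0.9473 and p2 = 0.8473 (a 10-point drop) gives n = 143.5.
- p1 = 0.9473 and p2 = 1 (a rise to 100%) gives n = 143.8.

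The stated size therefore does not show which question it was meant to answer.

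**2. Largest deficit that stays non-significant.** For a success/failure outcome, the Mann-Whitney test is essentially the two-proportion z test. MTA counts are set near 94.73%. The test is z = d / √(2p̄(1−p̄)/n), with Wald 95% CI d ± 1.96·√(p1(1−p1)/n + p2(1−p2)/n).

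| Analysed per arm | MTA | BBio | BBio − MTA (points) | p | 95% CI (points) |
|---|---|---|---|---|---|
| 143 | 135 (94.4%) | 126 (88.1%) | −6.3 | 0.060 | −12.8 to +0.2 |
| 187 | 177 (94.7%) | 167 (89.3%) | −5.3 | 0.057 | −10.8 to +0.1 |
| 234 | 222 (94.9%) | 211 (90.2%) | −4.7 | 0.053 | −9.4 to +0.05 |

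For the first row, p̄ = 261/286 = 0.9126, the null standard error is 0.0334, and z = −0.0629/0.0334 = −1.88. The Wald standard error is 0.0332, so the lower limit is −0.0629 − 1.96 × 0.0332 = −0.128. Newcombe lower limits for the three rows are −13.2, −11.1 and −9.7.

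**3. Chance of retaining the null when BBio is truly worse.** This is 1 − Φ[(δ − 1.96·SE0)/SE1], where δ is the true deficit, SE0 the standard error under the null and SE1 that under the alternative.
- δ = 10 points, n = 143: (0.100 − 1.96 × 0.0359)/0.0354 = 0.84, so 20%.
- δ = 10 points, n = 187: (0.100 − 1.96 × 0.0314)/0.0310 = 1.24, so 11%.
- δ = 10 points, n = 234: 5%.
- δ = 7.5 points: 40% at 143 and 28% at 187.

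**4. What the planned size could support as non-inferiority.** Power = Φ[(M − δ)/SE − 1.96] at one-sided 2.5%. The margins M are illustrative, since the document gives none.

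| Margin M | True deficit δ | n = 143 | n = 187 |
|---|---|---|---|
| 10 points | 0 | 97% | 99% |
| 7.5 points | 0 | 81% | 90% |
| 7.5 points | 2 points | 48% | 59% |
| 5 points | 0 | 47% | 58% |

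For example, M = 7.5, δ = 0 and n = 143 gives SE = √(2 × 0.9473 × 0.0527/143) = 0.0264, then 0.075/0.0264 − 1.96 = 0.88, so 81%. A 5-point margin would need 314 per group for 80% power.

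**The case against.** The strongest reply is that the Background sentence is only a loosely worded null of no difference. The stated aim is to evaluate pulp repair, the sample size is framed around detecting differences, and the tests match that framing. A reader might infer that the protocol commits to reporting a non-significant result as equivalence. It does not: no section states such a rule, and the point rests on what the wording invites. A reader might also infer that non-inferiority was the intended design. The handling and cost rationale makes that plausible, but the document does not establish it, and 143 per group fits a rise to 100% as well as a 10-point fall.

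Three further replies stand in part.
- An interval is planned. In the 143-per-arm example the odds ratio is (126 × 8)/(17 × 135) = 0.44, 95% CI 0.18 to 1.05, which visibly fails to support comparability. The plan is thus not confined to p-values, but nothing links that interval to a conclusion.
- It is tempting to say that BBio could be more than 10 points worse after any non-significant result. That overstates it. The 10.8 and 12.8 are confidence limits at the most extreme non-significant results, where the observed deficits are 5.3 and 6.3 points. With all 234 per arm analysed, the limit is about 9.4.
- It is also tempting to say that a false conclusion of comparability is controlled only at 20%. That figure depends on a 10-point effect that the Sample size section never states, and on 143 rather than 187 analysed.

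A later analysis plan could add a margin. It would then conflict with the hypothesis and tests stated here, so this wording would still need to change.

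**Conclusion.** The point holds as a mismatch between hypothesis and analysis. Comparability is placed in the null, and the stated difference tests and unanchored odds ratio cannot establish it. With 143 to 187 analysed per arm, non-significance is compatible with an observed deficit of about 5 to 6 points and with 95% limits out to 10.8 to 12.8 points. These figures assume two-sided 5% tests, MTA success near 94.73% and equal arms.

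The documents do not support the stronger claim that the planned size already secures a non-inferiority conclusion. That would need a margin they do not give and true rates that are nearly equal. At a 7.5-point margin, power falls from 81% to 48% (143) or from 90% to 59% (187) if BBio is truly 2 points lower.

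**What to change.** In Background, restate the null as no difference in success between BBio and MTA. In Statistical methods, declare that a non-significant result will not be read as comparability, and add the BBio minus MTA difference in success with its 95% CI. This costs a few sentences and no patients.

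If comparability is the conclusion the sponsor wants, state a non-inferiority hypothesis for one named success endpoint at one named time point, with a margin justified before analysis. Conclude non-inferiority only if the lower limit of the two-sided 95% CI for BBio minus MTA lies above minus the margin. Restate the power in Sample size for that margin, and show how it changes if BBio is slightly worse.

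The cost of this second route is justifying the margin. The planned size gives adequate power only for margins of about 7.5 to 10 points with near-equal true rates. A margin near 5 points would need more participants. Non-inferiority also does not protect against anything that blurs the difference between the groups, since that favours the new material under this hypothesis too.

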## Methods/design

### Study design

In primary teeth, vital pulp therapy goals are the pulp tissue regeneration and the maintenance of the physiological process of deciduous tooth exfoliation. Despite its biocompatibility, MTA has a longer setting time, difficult handling, high cost, and potential for tooth discoloration. Thus, this study aims to evaluate clinically and radiographically the pulp repair after the use of a new dentin-pulp biostimulation chitosan membrane in primary teeth with deep occlusal and occlusoproximal cavities reaching more than 3/4 of the total thickness of carious dentin evaluated by periapical radiograph, with at least two thirds of root length. This will be a double-blinded parallel-group randomized controlled trial composed of two groups: group 1 (G1—control), teeth treated with mineral trioxide aggregate (MTA), and group 2 (G2—experimental), teeth treated with the new dentin-pulp biostimulation chitosan membrane.

Before study group assignment, the allocation concealment will be performed to trial participants in sequentially numbered, sealed envelopes. This closed envelope will include a randomization number. Allocation concealment will be ensured, as the team responsible will not release the randomization number until the patient has been recruited into the trial. The operator will open the envelope and will find the treatment condition to be conducted in the patient. The operator then gives the information about treatment allocation to the patient. The team responsible for recruitment is not allowed to receive information about the group allocation.

One primary tooth per patient will be randomly allocated in each group. If the patient has more than one tooth to include in the study, the tooth closest to the inclusion criteria will be chosen. The allocation criteria will be the cavity type (occlusal and occlusoproximal) and the child’s age. Group allocation will be randomized through computerized stratified sampling (Microsoft Excel®), independently, that is, the patients and legal guardians will remain blinded to intervention group status. Randomization will occur close to the moment of the intervention [18]. Blinding the operator during the allocation sequence and application step will not be possible. The intervention group identifier will be assigned at random and will not be identified during data analysis, that is, the examiners will remain blinded.

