### Eligibility: inclusion and exclusion criteria

Inclusion criteria will comprise children aged from 5 to 9 years, from both genders, with one restorable maxillary/mandibular first/second primary molar with deep occlusal and occlusoproximal cavities reaching more than 3/4 of the total thickness of carious dentin evaluated by periapical radiograph, with at least two thirds of root length. Exclusion criteria comprised no history of spontaneous pain, internal/external root resorption, fistula/abscess, and lesion at furcal area, and any sign of mobility [1, 2, 28–31]. Also, by the time of clinical procedure, hemostasis will be checked and must occur within 5 min after coronal pulp exposure [28–31]. Exclusion criteria will be the presence of systemic diseases, history of allergic reaction to dental materials, and lack of hemostasis 5 min after coronal pulp exposure (Fig. 1).

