### Interventions

#### Clinical procedures

All clinical procedures of this study will be performed by one previously trained and calibrated operator (post-graduate student). A detailed anamnesis and clinical examination will be performed. Next, an intraoral clinical examination with the aid of dental mirror and air jet will screen eligible molars. Then, a periapical radiograph of the eligible primary molars will be taken to verify the furcal conditions. Satisfying all inclusion criteria of the study and after informed consent is given, treatment will be randomly provided in the second visit, according to previously described allocation. The patient and legal guardians will remain blinded regarding the treatment type [32].

After tooth prophylaxis with rubber cup and prophylactic paste (Herjos Tutti Frutt, Vigodent, São Paulo, Brazil), washing, and drying, local anesthesia will be applied (articaine 4% + epinephrine 1:100.000) [28–31]. The cavity preparation will be performed under rubber dam isolation, using water-cooled diamond burs, and caries will be completely removed from the lateral walls and enamel-dentine junction with the aid of low speed round burs (KG Sorensen®, São Paulo, Brazil). The pulp chamber roof will be removed with the aid of round diamond burs (1014-1015) at high speed under copious irrigation. The coronal pulp will be removed with the aid of hand excavators. Pulp vitality will be checked by cut resistance, red color, and hemostasis after 5 min. If necessary, constant irrigation will be performed with sterile saline solution. Pulp stumps will be dried with sterile cotton pellets, and the capping material will be applied according the assigned group [28–31]:

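### Release of the allocation is tied to recruitment and not to the intra-operative hemostasis check, so exclusion after randomisation by the unblinded operator is not ruled out

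*Protocol article*

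**What the plan says.** Under Study design, the protocol article describes sealed, numbered envelopes and states that "the team responsible will not release the randomization number until the patient has been recruited into the trial". It continues: "The operator will open the envelope and will find the treatment condition to be conducted in the patient", and then "The operator then gives the information about treatment allocation to the patient". On timing it adds "Randomization will occur close to the moment of the intervention". On masking it concedes that "Blinding the operator during the allocation sequence and application step will not be possible".

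Under Eligibility, the article requires that "by the time of clinical procedure, hemostasis will be checked and must occur within 5 min after coronal pulp exposure", and it lists "lack of hemostasis 5 min after coronal pulp exposure" among the exclusion criteria, with a reference to Fig. 1.

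Under Clinical procedures, one operator carries out all procedures. Once the inclusion criteria are met and consent is given, "treatment will be randomly provided in the second visit, according to previously described allocation". Anesthesia, cavity preparation, coronal pulp removal and the hemostasis check are described after that sentence. The capping material of the assigned group then follows.

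**The concern.** Concealment protects a trial only up to the moment the allocation is opened. Eligibility should therefore be complete by then. Here the stated release point is recruitment, while one eligibility criterion remains open until the pulp has been exposed. The person who judges that criterion also opens the envelope and cannot be blinded.

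The criterion is prognostic by the plan's own account, because hemostasis is one of three signs used to judge pulp vitality, with cut resistance and color. If teeth with doubtful hemostasis were excluded more readily in one arm, that arm would keep the better pulps and its success rate would rise without any effect of the material. The blinded examiners at 12 and 24 months cannot correct this, since they never see the excluded teeth. The number randomised would also differ from the number treated, for a reason that may depend on the arm.

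**Working it through.** **Order of events.** No figure in the plan settles this point, so the sections are set side by side.

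| Step | Section | What is fixed |
|---|---|---|
| Release of the number | Study design | Not before recruitment; no link to hemostasis |
| Opening of the envelope | Study design | By the treating operator, who then informs the patient |
| Timing of randomisation | Study design | Near the intervention; before or after pulp exposure is not stated |
| Random treatment | Clinical procedures | Second visit, after inclusion criteria and consent; written ahead of the operative steps |
| Hemostasis check | Eligibility; Clinical procedures | During the procedure, after pulp exposure; no separate or blinded assessor named |
| Failure of the check | Eligibility | Exclusion |

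The only stated trigger for release can be met before eligibility is complete. An envelope opened just before anesthesia would satisfy every sentence on timing, including "Randomization will occur close to the moment of the intervention". The plan as written therefore permits exclusion with the arm known.

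**Possible size.** The one input from the plan is the 94.73% success rate for MTA (Sample size). The rest are assumptions for illustration:

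- both materials have the same true success, 0.9473;
- a fraction b of teeth has borderline hemostasis, b = 0.05 or 0.10;
- success among those teeth is s, from 0.60 to 0.80;
- all of them are excluded in one arm and none in the other.

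Observed success in the arm that excludes is (0.9473 - b × s) / (1 - b). The spurious difference is that value minus 0.9473.

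| b | s | Calculation | Observed success | Spurious difference (points) |
|---|---|---|---|---|
| 0.05 | 0.80 | 0.9073 / 0.95 | 95.51% | 0.8 |
| 0.05 | 0.70 | 0.9123 / 0.95 | 96.03% | 1.3 |
| 0.05 | 0.60 | 0.9173 / 0.95 | 96.56% | 1.8 |
| 0.10 | 0.80 | 0.8673 / 0.90 | 96.37% | 1.6 |
| 0.10 | 0.70 | 0.8773 / 0.90 | 97.48% | 2.7 |
| 0.10 | 0.60 | 0.8873 / 0.90 | 98.59% | 3.9 |

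The control failure rate is 100 - 94.73 = 5.27%. In the arm that excludes, observed failure would fall to between 100 - 95.51 = 4.49% and 100 - 98.59 = 1.41%. Excluding half of a 10% borderline group gives the same result as excluding all of a 5% group with the same success. If both arms exclude alike, the spurious difference is zero.

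The planned numbers of teeth, 143 and 234 per group, do not enter this calculation.

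**The case against.** The strongest reply is that the order is inferred. A reader might take the article to say that the envelope is opened at recruitment and hemostasis judged afterwards. It does not say so. The recruitment sentence sets only an earliest time. Randomisation near the intervention fits either order, and so does random treatment after the inclusion criteria are met, because the Eligibility section states the hemostasis requirement beside the inclusion requirements. The operative steps are the same in both arms until the material is placed, so the allocation is not needed earlier. Informing the patient is weak evidence of timing, since the same section says that patients and guardians stay blinded. Fig. 1 is cited at the hemostasis exclusion and is not shown. All of this stands, and it is why the point is that the plan fails to exclude the faulty order, not that it prescribes it.

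It is also fair that hemostasis is checked before any study material is placed and has a stated time limit. Bias therefore needs both early opening and exclusions that differ by arm. That limits the claim to a risk.

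A reader might also set the bias against the difference that 143 teeth per group was meant to detect. The Sample size section gives no success rate for the membrane, no difference and no margin, so that comparison is not available.

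The reply that this is detail left to a fuller document is less convincing. The article does state a release point for the allocation, and that point does not fit its own eligibility rule.

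**Conclusion.** The point holds as a gap in the sequence. Release is tied to recruitment, an exclusion criterion is judged mid-procedure by the single unblinded operator who opens the envelope, and nothing places opening after the check. The natural reading of Study design and Clinical procedures permits exclusion of poor-prognosis teeth after randomisation with the arm known. The documents do not show that this will happen or in which direction it would act.

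The illustrated bias of about 0.8 to 3.9 points rests wholly on the assumed borderline fraction (5-10%), the assumed success in those teeth (60-80%) and exclusion in one arm only. Less one-sided behaviour gives less. Against 5.27% expected failure in the control group, even the middle of that range could affect the comparison.

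**What to change.** Reconcile Study design, Eligibility and Clinical procedures with one explicit sequence: the operator opens the next numbered envelope for the stratum only after hemostasis and every other eligibility criterion have been confirmed and recorded. Teeth that fail the check are logged as screened and not randomised. The hemostasis rule stays as it is.

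The article gives August 2020 (Study setting) or September 2020 (Trial status) as the planned end of recruitment and was published in October 2020, so the new sequence may come too late for many teeth. For any envelope already opened before the check, report hemostasis exclusions by arm and keep those teeth in the randomised denominator.

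The cost is a change of wording and a small chairside burden: the envelope must be opened mid-procedure with both materials ready.

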### Outcomes

#### Clinical and radiographic evaluations

The teeth will be clinically and radiographically evaluated at 12 and 24 months regarding the pulp response [28–30]. During the follow-up assessment, the following clinical criteria will be verified: spontaneous pain; any signs of mobility, sensitivity to percussion, abscess/fistula, gingival swelling not caused by poor oral hygiene, and restoration failure. The radiographic criteria will include presence/absence of internal/external resorption, signs of furcal impairment, advanced rhizolysis stage, and restoration failure including fracture and loss. Two previously trained and calibrated blinded examiners will perform the clinical and radiographic assessments. Examiners will be previously trained and calibrated in relation to the clinical and radiographic criteria in a pilot study, based on previous studies [30, 31, 33]. Inter- and intra-examiner reliability will be verified by casual and systematic error [36]. The examiners will fill in a form with all data for further analyses of the results.

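### The Study design section has the operator tell the patient the allocation, which contradicts the stated blinding of patients and guardians and the double-blinded label

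*Protocol article*

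**What the plan says.** All references are to the protocol article.

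- **Label.** Study design: "This will be a double-blinded parallel-group randomized controlled trial composed of two groups".
- **Envelope step.** Study design, on allocation: "The operator will open the envelope and will find the treatment condition to be conducted in the patient". The sentence that follows is "The operator then gives the information about treatment allocation to the patient".
- **Patient and guardian blinding.** The next paragraph of Study design says that "the patients and legal guardians will remain blinded to intervention group status". Clinical procedures repeats it: "The patient and legal guardians will remain blinded regarding the treatment type".
- **Operator.** Study design: "Blinding the operator during the allocation sequence and application step will not be possible".
- **Assessors.** Clinical and radiographic evaluations: "Two previously trained and calibrated blinded examiners will perform the clinical and radiographic assessments". The section on measuring the dentin barrier names a blinded measurer, and the data collection section has blinded researchers completing the case report forms.
- **Outcomes.** The clinical criteria at 12 and 24 months begin with "spontaneous pain; any signs of mobility, sensitivity to percussion" and go on to signs that an examiner can observe. The radiographic criteria and the barrier thickness are read from films.

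**The concern.** One sentence instructs the operator to reveal the allocation, and two others say that the patient will not know it. With the operator unblinded by necessity, a double-blinded label needs the patient side as well as the assessor side to be blind. The disclosure step, if carried out, removes the patient side.

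Two things are at stake. First, part of the clinical outcome depends on the child or guardian. Spontaneous pain is learned from their history, and percussion sensitivity depends partly on how the child reacts. A family that knows whether the tooth received the new membrane or the established material may report differently. Second, an informed family can tell the examiner at the 12- or 24-month visit, which would weaken the one layer of blinding that the clinical assessment would still have. A reader of the eventual results could not tell from this text who was blinded.

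**Working it through.** No calculation applies, because the point is whether the blinding statements are consistent. I set them side by side.

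1. **What the operator knows.** The envelope is said to contain a randomisation number, but the text then says that the operator finds the treatment condition in it. The operator therefore holds the actual treatment and not only a code.
2. **What is passed on.** The disclosure sentence speaks of information about treatment allocation. Nothing in the article limits this to a number or a neutral code.
3. **What patients are meant to know.** Study design and Clinical procedures both say that patients and guardians remain blinded, to group status in one and to treatment type in the other.
4. **Can 2 and 3 both hold?** No. A patient told the treatment allocation is not blinded to group status. No other section qualifies either statement, and both are current text.
5. **Who is blind under each reading.**

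| Role | Disclosure step followed | Disclosure step not followed |
|---|---|---|
| Operator | not blind | not blind |
| Patient and guardian | not blind (guardian if also told) | blind |
| Clinical and radiographic examiners | blind, unless told by the family | blind |
| Dentin barrier measurer | blind | blind |
| Data collectors | blind | blind |

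6. **Which outcomes are exposed if the step is followed.** Spontaneous pain is the most exposed, because it comes from the child's or guardian's account. Percussion sensitivity is less exposed: a blinded examiner elicits it, but the child's reaction enters. Mobility, abscess or fistula, swelling and restoration failure are observed by the examiner and are affected mainly if the examiner is unblinded. Radiographic criteria and barrier thickness do not depend on the child's report.
7. **Timing.** Study setting plans recruitment to August 2020, and Trial status plans it to September 2020. The article is dated 22 October 2020. On the planned dates, most or all treatment visits were over by publication, although Trial status still calls recruitment incomplete. The first patient entered in December 2019, so the first 12-month visit would fall in December 2020, after publication. A correction could therefore come too late for the treatment step but still in time for the follow-up assessments.

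**The case against.** The strongest reply is that the sentence is a drafting slip. The double-blinded label and two explicit statements favour patient blinding, and only one sentence goes the other way. Clinical procedures describes the treatment visit with no disclosure step and repeats the blinding. That is a fair argument, and it stands as far as it goes: the text proves an inconsistency and does not prove that any family was told. It does not remove the point, because the disclosure sentence is the only one that says what the operator does with the information after opening the envelope.

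A second reply is that only a code might be handed over. The mention of a randomisation number in the envelope gives this some colour. The wording about the treatment condition and the treatment allocation does not support it.

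A third reply is that several layers of blinding remain and most criteria are observed rather than reported. This stands, and it limits the reach of the concern to spontaneous pain, partly to percussion, and to possible unblinding of the clinical examiners.

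A reader might also go further and put a number on the bias, for example by asking how far two or three differently reported pain events would move an arm's failure rate. The documents do not support this. They give no rate of pain events. The 94.73% success in the Sample size section is for clinical and radiographic success, not for pain. The same section states no target difference against which a shift could be judged. Any assumed number of differential events would be invented.

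**Conclusion.** The contradiction is real and unresolved within the article. As written, the procedure removes the patient blinding that the same section promises, and the double-blinded label cannot be relied on until this is settled.

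The consequence is conditional. If the step was followed, it applied to every child treated under it. The trial would then be blinded only at the level of examiners, barrier measurer and data collectors, with spontaneous pain and, less so, percussion sensitivity open to reporting bias. If it was not followed, the fault is one of wording only. No numerical effect on the results can be derived.

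A reader might infer that the trial was in fact unblinded or that its outcomes are biased. The text does not establish either. The case for correction rests on the contradiction itself, and on the assumption that patient here means the child or family being treated.

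**What to change.** Reconcile the statements so that the text says plainly who is blinded, to what, and until when.

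- **If patients were meant to be blinded:** delete the disclosure sentence and state that the allocation is withheld from child, guardian and examiners through the 24-month assessment.
- **If disclosure was intended:** remove the two statements of patient and guardian blinding and the double-blinded label.
- **In either case:** because recruitment may already be complete, establish from the operator and the trial records what participants were told, and report it.
- **If disclosure occurred:** ask families not to reveal the allocation to the examiners at follow-up, describe the trial as assessor-blinded only, and interpret spontaneous pain and percussion sensitivity as unblinded criteria.

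The cost is small: a wording change, a check of what was done, possibly a short instruction to families before follow-up visits, and perhaps a less favourable blinding label. Sample size and analysis are unaffected.
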